**Figure 1 F1:**
[figure not shown]
Schematic overview of the OptiNeoCare study. eCRF, electronic case report form.

In all participating centres, in the event of severe perinatal asphyxia, prospective data collection will be initiated following an interview between the family and the case’s referring physician or local study coordinator. During this interview, study information will be provided, and non-opposition to participation will be documented. Data collection will be carried out by the local study investigator at the maternity unit—potentially assisted by a clinical research technician (CRT) as early as possible after the event, no later than within the first week.

This prospective data collection will include:

Maternity unit: labour and delivery roomMaternal and obstetric data: maternal medical history, prenatal care and risk factors associated with perinatal asphyxia.Intrapartum obstetric and anaesthetic data: partogram, fetal heart rate monitoring and timestamped records of decisions and clinical interventions.Neonatal data: initial clinical examination, detailed and timestamped description of delivery room management and administered treatments.Organisational data: personnel present, structure and workflow, workload, available and completed documentation.Neonatal transportTimestamped information on management, interventions and neonatal parameters during transport.Organisational data: personnel involved, travel distance and duration.Neonatal intensive careTimestamped data on management, treatments and neonatal status on arrival and during the first 24 hours of life.Organisational data: personnel present and workload.

Following the inclusion of cases, a random selection of medical records will be subject to expert review. One in four cases will be randomly selected using the CleanWeb software. These ‘expert review’ cases will undergo a confidential enquiry by two assessors (an obstetrician and a neonatologist) who will visit the participating centres. Data will be collected from the medical records, available institutional documents and interviews with the healthcare professionals involved in the case. All collected information will be entered into the CleanWeb eCRF.

The data will be submitted to the OptiNeoCare study steering committee, which will verify data anonymisation before transmitting them in a digital format to two expert reviewers. These reviewers will be responsible for preparing the expert panel meeting related to the case. If needed, the reviewers may request additional information from the study steering committee, which will then forward the clarifications to the assessors.

During the expert panel meeting, the case files will be made available to the experts in both paper and electronic formats. The discussions will be summarised in a report, which will be electronically validated by the experts and sent every 4 months to the participating centres via the internet. This report will be accessible through a dedicated website for the study.

The MMR reports recorded in the e-CRF will be reviewed by the expert panel after the end of the inclusion period. The panel will summarise the main qualitative and quantitative findings in a comprehensive anonymised report.

### Statistical methods

#### Descriptive analysis

Quantitative variables will be described using counts, means, SD, medians, quartiles, ranges and the number of missing values. Qualitative variables will be presented as counts, percentages and the number of missing values.

The primary outcome (the frequency of optimal management) will be described and factors associated will be analysed using a logistic regression model. Secondary outcomes will be analysed using the same type of model as for the primary outcome. For continuous outcomes, mixed linear models will be used. An analysis of the determinants of suboptimal care will be performed using multivariable logistic regression to identify variables independently associated with suboptimal management, adjusting for relevant covariates. Given the method used to assess the primary outcome (expert classification of care quality), no missing data are expected for this variable. However, in rare cases where experts are unable to decide, a ‘cannot assess’ category will be available. Some missing data in the medical records will be considered meaningful and indicative of suboptimal care (eg, absence of documented clinical examination in the medical file). In such cases, the newborn will be classified as having received suboptimal care. For other variables, multiple imputation using chained equations may be applied to address missing data.

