### Primary outcome measure

The primary outcome will be the frequency of optimal versus suboptimal care observed during maternal and neonatal management in cases of moderate to severe HIE or neonatal death related to severe perinatal asphyxia.

Suboptimal care will be classified based on data entered in the electronic case report form (eCRF), using the framework described by Leape *et al*,^13^ encompassing the following categories:

Diagnostic errors (errors or delays in diagnosis; failure to perform indicated diagnostic tests; use of outdated diagnostic methods; misinterpretation of diagnostic test results).Therapeutic errors (errors in procedural performance; errors in medication administration; dosage errors; avoidable delays in treatment or in responding to abnormal test results; provision of inappropriate care).Preventive failures (lack of indicated prophylactic treatment; inadequate monitoring or follow-up of treatment).Other systemic or organisational failures (communication failures; equipment deficiencies; other system-level failures).

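### Scoring certain missing chart items as suboptimal care can only raise the suboptimal share; cases suboptimal on documentation alone should be flagged and results shown both ways

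*Protocol article*

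**What the plan says.** The primary outcome is the frequency of optimal versus suboptimal care (Primary outcome measure). The handling of missing data is in Statistical methods, Descriptive analysis. There the outcome is described as an expert classification. A category for cases that cannot be assessed is kept for use "in rare cases where experts are unable to decide". The article then adds: "Some missing data in the medical records will be considered meaningful and indicative of suboptimal care". The one example given is "absence of documented clinical examination in the medical file". The consequence is fixed: "In such cases, the newborn will be classified as having received suboptimal care".

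The same section fits a multivariable logistic regression to suboptimal management to look for its determinants. The section on determinants names maternity unit level and timing of care, with night shifts as its example. The Abstract plans to relate care quality to neonatal outcomes, and a secondary outcome compares the eCRF and local review with the confidential enquiry.

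Two further statements bear on the point, both in Study organisation. Enquiry assessors use the chart, institutional documents and "interviews with the healthcare professionals involved in the case". The organisational data collected on every case include which documentation was available and completed.

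**The concern.** An item missing from the chart may mean that the act was not done, or that it was done and not written down. The rule gives both the same code. It can move a case from optimal to suboptimal and never the reverse. The suboptimal share is therefore pushed up, and the optimal share down, by every adequately managed case with a qualifying gap.

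Three results could be affected. The headline frequency will naturally be read against the roughly 50% from the literature that the Sample size section uses. The determinants and neonatal-outcome models use the same classification. The concordance analysis compares two sources that may differ in how far they can see past the chart.

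**Working it through.** **The plan's own figures.** Sample size gives 336 infants, one in four sent to enquiry, and 50% suboptimal.
- 336 / 4 = 84, and 0.5 × 84 = 42.
- 336 − 84 = 252, and 0.5 × 252 = 126.

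Both stated counts (42 and 126) reproduce. The expected total is 42 + 126 = 168 of 336.

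**Effect on the frequency.** Let p be the true suboptimal share (0.50, from the plan) and m the fraction of adequately managed cases with a qualifying gap. The document gives no m, so a range is assumed. The observed share is q = p + (1 − p)m.

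| Assumed m | q | Expected count of 336 | Expected count of 84 |
|---|---|---|---|
| 0% | 50.0% | 168.0 | 42.0 |
| 5% | 0.5 + 0.5 × 0.05 = 52.5% | 176.4 | 44.1 |
| 10% | 0.5 + 0.5 × 0.10 = 55.0% | 184.8 | 46.2 |
| 20% | 0.5 + 0.5 × 0.20 = 60.0% | 201.6 | 50.4 |

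**Compared with sampling error.** The 95% half-width at 50% is 1.96 × √(0.25/n): 5.3 points at n = 336 and 10.7 points at n = 84. The shift (1 − p)m equals the half-width when m is about 11% (0.053/0.5) or 21% (0.107/0.5) respectively.

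**Effect on a determinant.** Take two strata with the same true care (p = 0.50 in each) and gap fractions a and b. The odds ratio is [q_b/(1 − q_b)] / [q_a/(1 − q_a)].
- 5% versus 5%: (0.525/0.475) / (0.525/0.475) = 1.00.
- 5% versus 10%: (0.55/0.45) / (0.525/0.475) = 1.11.
- 5% versus 20%: (0.60/0.40) / (0.525/0.475) = 1.36.

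For 5% versus 20%, with strata of equal size and a two-sided 5% test (normal approximation), the chance of a significant result with no difference in care is about 28% at 168 versus 168 and about 11% at 42 versus 42. With equal gaps it stays at 5%.

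**Effect on concordance.** No arithmetic applies, and two readings of the text are possible. If the rule is applied to the medical file exactly as worded, an interview does not change the code, and the rule treats enquiry and in-situ cases alike. If assessors may use interviews to establish that an unrecorded act took place, the same chart could be optimal under enquiry and suboptimal in situ. The article does not say which applies.

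**The case against.** The strongest reply is that this is a choice of construct. The plan may reasonably hold that leaving an essential examination unrecorded is itself a failure of care. The error framework in Primary outcome measure is broad, ending with "communication failures; equipment deficiencies; other system-level failures". On that view there is no bias, because the true status includes charting. This stands in part, and it is why the rule can remain for the primary figure. It does not remove the need to separate the two: the listed categories do not name documentation, and a reader cannot tell how much of the result is charting and how much is care delivered.

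The rule is also limited. It covers only some missing items, and it sits within an expert classification. The category for undecided cases serves a different purpose, so having both provisions is not a contradiction.

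A reader might infer that the rule creates false determinants because records are thinner at night, in emergencies or in certain units. The document does not support that. Nothing in it says that completeness varies in this way, emergency is not among the determinants it names, and equal gaps give an odds ratio of 1.00.

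A reader might also infer that the rule certainly acts differently in the two components. That is not established either, and it conflicts with reading the rule as automatic. In-situ cases have some protection too: collection at the unit within the first week, automated checks for missing values, and queries resolved with local teams (Data quality control). These are weaker than staff interviews, but they count for something.

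Finally, the list of qualifying items and any sensitivity analysis may be in the full protocol or analysis plan. Their absence from the article is not held against it. The point rests on the rule that the article does state.

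**Conclusion.** The point holds in a limited form. The one-way effect on the primary frequency follows from the wording of the rule and needs only that some adequately managed cases have a qualifying gap. Its size depends on m, which is unknown: 2.5 to 10 points for an assumed 5% to 20%, at the planned 50%. It reads as inflation only if the frequency is taken to measure care delivered rather than care and charting together.

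The effect on determinants is conditional on gaps differing by a studied factor, which is an assumption: 1.36 for 5% versus 20%, and nothing if gaps are equal. The same condition applies to the neonatal-outcome model. The effect on concordance is a possibility that depends on how interviews are used. None of this invalidates the study. It is a cheap improvement in what the results can be taken to mean.

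**What to change.** Keep the rule for the primary figure. Add one eCRF flag for cases that are suboptimal on documentation alone, as their own subcategory, and report their number. Then give the primary frequency, the determinants and neonatal-outcome models and the concordance analysis twice: with these cases counted as suboptimal, and with them not so counted but still in the denominator.

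For the frequency, the two figures bound the answer as far as this rule is concerned. For example, at p = 50% and an assumed m of 20%, if every flagged case had in fact received adequate care, they would be 60% and 60% − 10% = 50%. For odds ratios they show sensitivity and are not strict limits, because the truth may lie differently in different strata.

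Do not remove flagged cases from the main models outright. Some undocumented examinations were truly not done, and dropping those cases would discard real omissions and could bias the result the other way. It would also help to state whether an interview may establish an unrecorded act in enquiry cases.

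The cost is one flag, which the documentation data already collected should largely support, an extra set of results, and a second, lower headline figure to explain.

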#### Sample size

The prevalence of HIE is estimated at 1–2 per 1000 live births.^20^ In the national French-based Lytonepal cohort, which included only cases of moderate to severe HIE, the prevalence was estimated at 0.90 per 1000 live births (95% CI: 0.84 to 0.95).^21^ For the OptiNeoCare study, we estimated a prevalence of 1 per 1000 births, as we also include intrapartum stillbirths and cases of HIE initially missed at birth but subsequently hospitalised for neurological symptoms. These cases were not captured in the Lytonepal cohort.

Furthermore, according to the literature, suboptimal care in the management of HIE is reported in approximately 50% of cases.^7 11 22^ We therefore hypothesise that about 50% of the care provided in cases of severe perinatal asphyxia is suboptimal. The study will include 12 perinatal centres covering a population with approximately 340 000 births per year. Level III maternity units and their associated centres are expected to include, on average, 1.5 newborns per month, corresponding to a total of approximately 336 infants over a 12-month inclusion period.

This recruitment will allow us to conduct a confidential enquiry on 84 infants, enabling the identification of suboptimal care in approximately 42 cases. In addition, the in-situ component of the study will provide data on the remaining 252 cases, allowing us to identify and describe around 126 instances of suboptimal care.

### Data quality control

Several procedures will be implemented to ensure data quality throughout the study. Standardised data collection forms and a centralised (eCRF) system (CleanWeb) will be used to minimise variability and entry errors. Data will be entered by trained local investigators or CRTs at each site. Automated consistency and plausibility checks will be integrated into the eCRF to identify outliers, inconsistencies or missing values in real time. Regular data monitoring will be conducted by the coordinating centre to verify the completeness, accuracy and timeliness of data entry. Queries will be generated and resolved in collaboration with the local teams.

Additionally, expert case reviews will include cross-checking of clinical documentation, organisational records and interviews with care teams, ensuring a comprehensive and high-fidelity dataset. Finally, participating centres will be regularly contacted by the national coordinating team via email to report any occurrences of severe perinatal asphyxia. This will include both maternity units and the associated neonatal intensive care units (NICUs) and transport teams. The collected data (place and date of birth) will be cross-checked in the CleanWeb system to prevent duplicate case inclusion.

At the end of the study, a query will be submitted to the Centre d’épidémiologie sur les causes médicales de décès (*CepiDC*), a comprehensive national mortality database, to verify that all cases of neonatal death prior to transfer have been appropriately identified and reported.

## Ethics and dissemination

Our protocol has received approval from the Ethics Committee for Research in Obstetrics and Gynaecology (CEROG): CEROG 2023-OBS-1206

Hospitals have signed multicentre collaboration agreements. Participants (or their legal representatives) will be thoroughly informed about this study, receiving written information and having the option to oppose the collection of data related to their case. In accordance with Article L1121-1-1 of the French Public Health Code, no non-interventional research may be conducted on an individual who has objected to participation after having received the information required under Article L1122-1 of the same code. The guardians of the newborns and the public will not be involved in the study design. However, newborns will be recruited voluntarily during the enrolment phase. Participation will be entirely voluntary. The study results will be disseminated to guardians and the public through public health education initiatives, as well as neonatal brain injury conferences and academic journals.

This research falls within the scope of the ‘Reference Methodology for the Processing of Personal Data in Health Research’ (modified MR-004). The study sponsor, Assistance Publique–Hôpitaux de Paris, has signed a compliance commitment to this reference methodology.

All documents and data collected during the research will be securely stored and retained for up to 2 years following the final publication of the study results. In the absence of publication, data will be kept until the final research report is signed. Data management procedures follow established standards to ensure confidentiality, integrity and traceability. Only authorised members of the research team will have access to the data. No personal identifying information will be published.

This study is registered on ClinicalTrials.gov under the ID: NCT06322732.

## Discussion

Severe perinatal asphyxia at term is a critical condition caused by obstetric events or fetal heart rhythm abnormalities during labour, that can result in intrauterine or peripartum death (0.6/1000 births) or HIE (1.6/1000 live births),^1^ affecting ~1000 newborns annually in France. As an unexpected and urgent situation, immediate obstetric and neonatal management is crucial for the prognosis of the newborn.^23^ Despite advances like therapeutic hypothermia in the neonatal critical care unit,^3^ the prognosis for HIE newborns remains poor, with a neonatal mortality risk estimated at 15–20% and a disability rate among survivors at 30%.^4^ This issue is particularly acute given that since 2012, France has seen an increase in the paediatric mortality rate,^24^ primarily related to perinatal deaths. Since 2015, infant mortality has been higher than the European average,^25^ with France, which ranked third among the European countries, now ranking 20th.^26^ This marker is recognised as one of the recommended indicators of perinatal health in European countries.^27^ Knowing the incidence of severe perinatal asphyxia and understanding its determinants are important public health challenges.

One of the strengths of this prospective observational study lies in its comprehensive approach, encompassing the entire continuum of obstetric and neonatal care, including neonatal transport. This design enables the identification of potential challenges in the coordination of care from a multiprofessional perspective.

Another key strength is the involvement of all maternity units within participating perinatal networks, including public and private hospitals of various levels. This is particularly relevant for a condition such as perinatal asphyxia, which can occur regardless of the type of facility where delivery takes place. Furthermore, this inclusive approach allows for the identification of potentially suboptimal care practices in centres that are traditionally underrepresented in clinical research in France.

Finally, the geographical diversity of participating regions—including urban areas, rural settings such as Burgundy and mountainous regions like the Grenoble network—will contribute to a comprehensive assessment of care quality across contrasting healthcare environments.

Among the potential challenges, ensuring the completeness of case inclusion and verifying this completeness is of particular importance. To minimise missed inclusions, inclusion monitoring will be carried out through the perinatal network. This will involve: (1) contacting participating maternity units to identify any potentially eligible but non-included cases and (2) querying the NICUs to which these centres refer, as well as the SMUR neonatal transport units, both of which are centrally coordinated within the French perinatal network. In addition, neonatal deaths are recorded in a national mortality database (CepiDC), which will be used to identify potential cases of death occurring prior to transfer.

Finally, this pioneering study on suboptimal care in the obstetric and neonatal management of severe perinatal asphyxia will provide critical insights into the circumstances and determinants of care failures. Beyond its immediate findings, it aims to establish a sustainable, nationwide system for systematic case analysis. This initiative is intended to drive continuous improvement in the quality of perinatal care and ultimately reduce the burden of morbidity and mortality associated with this serious condition.
